**Materials and methods:**

A prospective observational diagnostic study will be conducted. Patients ≥ 18-year-old and requiring the insertion of an NGT will be recruited using a convenience sampling method from 39 general medical and geriatric wards, intensive care units, accident and emergency departments, and subacute/rehabilitation/infirmary wards in 21 acute or subacute/convalescent/extended care hospitals. ETCO_2_ detection by sidestream capnography, which indicates an airway intubation of an NGT when a capnogram waveform or an ETCO_2_ level > 10mmHg (1.33 kPa) occurs, will serve as the index test. The reference standards will be the X-ray performed and pH value of gastric aspiration (pH ≤ 5.5) after the index test. Each participant will be included only once. Sensitivity, specificity, positive predictive value, negative predictive value, and area under the receiver operating characteristic curve of capnography will be calculated to assess the diagnostic performance of capnography. The variability in diagnostic accuracy in participants with different characteristics will be explored by using chi-squared or Fisher’s exact tests. The time spent and the cost of the tests will be compared using the paired t-test. All statistical tests will be two-sided with a level of significance set at 0.05.

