## Introduction

Nasogastric tube (NGT) placement is a common practice in hospital settings for assessment, nutrition support, and administration of medication [1,2]. Unfortunately, misplacement of NGTs is common, with an estimated 60% of misplacements resulting in detrimental effects [3,4]. In fact, in over 80% of these misplacements the NGTs were placed in the respiratory tract, leading to serious pulmonary complications, including aspiration pneumonia or respiratory failure [4,5]. Chest/abdominal X-ray is the gold standard for verifying correct NGT placement in the stomach. However, radiography is not always available conveniently at the bedside [6]. Other methods for verifying NGT placement include biochemical measurements of aspirates for pH value or presence of bilirubin, trypsin or pepsin, spring gauge pressure manometer, magnetic detection, ultrasonography, auscultation, and visual inspection of aspirates [7–11]. Factors often compromised the accuracy of these methods include the inability to aspirate adequate fluids for testing, difficulty in visually differentiating the colour change in test strips, use of antacids, reflux of gastric contents, or patients with altered level of consciousness [7,8,11]. Therefore, a reliable and effective bedside test to verify NGT placement is required.

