To determine the applicability of ETCO_2_ detection in clinical settings, Cheng and Lee evaluated the diagnostic accuracy of colorimetric capnometry in verification of feeding tube placement in 26 patients (with 71 doubtful NGT placements) recruited from three medical extended wards in a public hospital in Hong Kong [13]. The specificity of the colorimetric capnometry was 98.6%, while the sensitivity could not be determined. A team of community nurses conducted a pilot study between March and April 2021 to examine the use of capnography in verifying correct NGT placement. Two devices were used, namely EMMA Capnograph and Rad-97 Pulse Co-oximeter. A total of 12 older adults (mean age 80.3 years, range 55–89 years old) residing in old age homes were recruited. Nine of them were receiving lansoprazole, and one was receiving famotidine. Of the 15 episodes of NGT insertion performed among the 12 older adults (seven used EMMA Capnograph and eight used Rad-97), none of the episodes detected ETCO_2_ and crisp waveforms after testing of tube placement in the stomach by the Whoosh test [13].

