#### Reference standard

The reference standard is the test, series of tests, or set of procedures used to determine the presence or absence of the target condition in individuals, which in this study is airway intubation of an NGT [25]. This study will use radiography (chest/abdominal X-ray) as the reference standard for determining the correct placement of NGTs. Radiology will be performed as soon as possible and interpreted by a physician. A repeat radiography will be performed if necessary. We will also use pH-Fix-4.5–10 to determine the pH value, and its accuracy is +/- 0.2 with minimum increments of 0.5. A pH of 5.5 or below indicates gastric placement [2].

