## Data analysis

The sample size is determined to give the study adequate precision to estimate the sensitivity and specificity of using capnography in detecting the placement of NGTs using the reference standards of measurement of radiography and aspirates for pH value. In anticipation of sensitivity and specificity of values greater than 90% [17], a sample size of at least 500 participants would be sufficient to estimate these parameters with a margin of error of at most ±3% at a significance level of 0.05. The sample size calculation was performed using PASS 16 (NCSS, Kaysville, USA). Eligible participants will be evenly recruited from the 39 participating wards/units. The target sample size will therefore be rounded up to 507 with 13 eligible participants per each of the 39 wards/units.

IBM SPSS 26.0 (IBM Crop., Armonk, NY) will be used to conduct the data analysis. Participants’ demographic and clinical characteristics will be presented by appropriate descriptive statistics, including mean ± standard deviation, median (inter-quartile range), and percentages for normally distributed, skewed continuous, and categorical variables respectively. Any cases with missing data on the index test or the reference standard results will be excluded from the test accuracy analysis. The true positives (i.e., NGT placements that are tested positive by both index test and reference test/s), false negatives (i.e., NGT placements that are tested negative by index test but positive by reference test/s), true negatives (i.e., NGT placements that are tested negative by both index test and reference test/s), and false positives (i.e., NGT placements that are tested positive by index test but negative by reference test/s) will be calculated, based on which the sensitivity, specificity, positive predictive value, and negative predictive value of the capnography test will be calculated with reference to a combination of X-ray and aspirate pH test using the following formulas:

$$\text{Sensitivity}:\;\text{True}\;\text{Positive}/\left(\text{True}\;\text{Positive}+\text{False}\;\text{Negative}\right)\times 100\%$$

$$\text{Specificity}:\text{True}\;\text{Negative}/\left(\text{True}\;\text{Negative}+\text{False}\;\text{Positive}\right)\times 100\%$$

$$\text{Positive}\;\text{Predictive}\;\text{Value}:\text{True}\;\text{Positive}/\left(\text{True}\;\text{Positive}+\text{False}\;\text{Positive}\right)\times 100\%$$

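### Accuracy is scored against an undefined combination of X-ray and aspirate pH, although the target condition is airway placement and pH is given only a gastric meaning

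*Protocol article*

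**What the plan says.** Under Reference standard, the target condition is stated as the one "which in this study is airway intubation of an NGT". The same section says: "This study will use radiography (chest/abdominal X-ray) as the reference standard for determining the correct placement of NGTs". It then adds aspirate pH as something also used, with a single interpretation: "A pH of 5.5 or below indicates gastric placement". No meaning is given there to a pH above 5.5.

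The abstract puts the two tests on an equal footing: "The reference standards will be the X-ray performed and pH value of gastric aspiration (pH ≤ 5.5) after the index test". Study design likewise names both as reference standards.

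Data analysis builds the two-by-two table from tests described as positive or negative on the reference. A false negative covers "NGT placements that are tested negative by index test but positive by reference test/s". All four accuracy measures "will be calculated with reference to a combination of X-ray and aspirate pH test". No either/both rule is given, and nothing says how a tube that X-ray shows in the stomach but whose aspirate reads above 5.5 is to be classified. The section also drops cases with a missing index or reference result.

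Two other sections matter. Procedures arranges an X-ray after the index and pH tests. Data collection records tube location as stomach, esophagus or tracheobronchial tree.

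**The concern.** The reference used for scoring should identify the target condition. X-ray location does this directly. The pH test answers a different question: a low value supports gastric placement, but a high value only fails to support it. The Introduction itself lists factors that compromise the bedside methods as a group, including failure to obtain aspirate and "use of antacids, reflux of gastric contents, or patients with altered level of consciousness". A gastric tube can therefore have a high pH, or no pH at all, without being anywhere near the airway.

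The effect depends on how the two results are combined, and the article leaves that open. In the most damaging case, the reported sensitivity would largely reflect gastric pH rather than capnography. Two planned uses of the data would then suffer as well. The comparison of accuracy by drug use could show an artefact, because acid suppression would itself create false negatives. The Discussion's aim of finding the best combination of tests would be partly circular, because pH would sit on both sides of the comparison.

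**Working it through.** **Inputs from the article.** N = 507, from 39 wards × 13 participants (Data analysis). True sensitivity Se = 0.96 and specificity Sp = 0.99, the pooled values from the updated meta-analysis (Introduction).

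**Assumed inputs, not in the article.** Airway prevalence: 2%, 5% or 10%. Share q of non-airway tubes with pH above 5.5: 2% to 20%. Capnography is taken to be independent of pH once true location is known, and X-ray is taken as correct.

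**The plan's own figure.** At a proportion of 0.90 and n = 500, the 95% margin is 1.96 × √(0.90 × 0.10 / 500) = 0.026, so the stated margin of at most 3 points is reproduced. It holds for each parameter only if all 500 enter that parameter's denominator.

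**Reading 1: either test positive makes the reference positive.** Let A be the airway tubes and G the others.

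Apparent sensitivity = [A × Se + G × q × (1 − Sp)] / (A + G × q)

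Example at 2% prevalence and q = 20%:
- A = 10.14, G = 496.86, G × q = 99.37.
- Reference positives: 10.14 + 99.37 = 109.51.
- True positives: 0.96 × 10.14 + 0.01 × 99.37 = 9.73 + 0.99 = 10.73.
- Apparent sensitivity: 10.73 / 109.51 = 0.098.
- True negatives: 0.99 × (496.86 − 99.37) = 393.51. False negatives: 109.51 − 10.73 = 98.78. Apparent NPV: 393.51 / 492.29 = 0.80.
- Against true location, NPV is (0.99 × 496.86) / (0.99 × 496.86 + 0.04 × 10.14) = 491.89 / 492.30 = 0.999.

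Apparent sensitivity across the assumed range:

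| Airway prevalence | q = 2% | q = 5% | q = 10% | q = 20% |
|---|---|---|---|---|
| 2% | 0.49 | 0.29 | 0.17 | 0.10 |
| 5% | 0.70 | 0.50 | 0.34 | 0.21 |
| 10% | 0.82 | 0.67 | 0.51 | 0.35 |

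Apparent specificity stays at 0.99, because the tubes left as reference-negative are all truly outside the airway. The damage falls on sensitivity and NPV.

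**Reading 2: both tests must be positive.** Sensitivity stays at 0.96. If a share r of airway tubes reads 5.5 or below, apparent specificity is [G × Sp + A × r × (1 − Se)] / (G + A × r). At 5% prevalence and r = 20%: (481.65 × 0.99 + 5.07 × 0.04) / (481.65 + 5.07) = 477.04 / 486.72 = 0.980. So pH changes almost nothing. A complete reference result, however, would then need an aspirate even from a tube in the airway, and the missing-data rule could remove airway tubes that yield none.

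**Reading 3: X-ray decides and pH only supports it.** The accuracy measures are unaffected, but the reference is then X-ray and the word combination in Data analysis is inaccurate.

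**X-ray location alone.** Expected sensitivity and specificity are 0.96 and 0.99 whatever q is. Precision for sensitivity rests on the airway tubes only: about 10, 25 and 51 at 2%, 5% and 10% prevalence. Exact 95% intervals are 0.69–1.00 (10/10), 0.80–1.00 (24/25) and 0.87–0.995 (49/51).

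**The case against.** The strongest reply is that the harm rests on a rule the article never states. A reader might infer that the protocol does misclassify correctly placed tubes and that sensitivity will collapse. The text does not support that as fact: nowhere is a pH above 5.5 said to make the reference positive, and under Readings 2 and 3 sensitivity is essentially unharmed. Reading 3 also fits the Reference standard section and the blinded reading of the X-ray in Procedures. How discordant results are classified could be set out in a fuller document that is not shown. This stands, and it makes the size of the effect conditional. It does not remove the mismatch, because the article states a combined reference for a target that one component does not measure. Reading 1 is also a natural one, since the abstract pairs X-ray with pH of 5.5 or below as joint standards, so that failing either could count as not correctly placed.

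A reader might also take the Introduction's pilot data ("Nine of them were receiving lansoprazole, and one was receiving famotidine", out of 12 patients) as this trial's own experience. They come from an earlier community-nurse pilot in old age homes, where placement was checked by the Whoosh test and no pH values are reported. The trial's own pilot is still to be done. The 10 of 12 show that acid suppression is plausible in such patients; they give no rate of high pH for hospital wards.

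Nor is every use of pH in a reference harmful. The article allows repeat radiography, so some films may not settle the position, and a low pH could then support gastric placement. The objection is to letting a high pH count as airway placement.

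**Conclusion.** The concern holds in conditional form. The stated reference for the accuracy analysis does not match the stated target condition, and the rule for combining its two parts is not given. If a pH above 5.5 can make the reference positive, apparent sensitivity falls from 0.96 to between 0.82 and 0.10 over the assumed ranges, 2% to 10% airway prevalence and 2% to 20% of non-airway tubes with high pH. Neither range comes from the article. If both tests must be positive, the estimates barely move, pH contributes almost nothing, and the remaining risk is selective loss of airway tubes without aspirate. None of the three readings gives a reason to keep pH in the reference for airway placement when X-ray location is already recorded. The wording should be corrected before the analysis.

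**What to change.** In the abstract, Study design, Reference standard and Data analysis, make X-ray location (tracheobronchial versus not) the sole reference for the airway-placement accuracy analysis. In Data analysis, replace the phrase about the combination with *with reference to X-ray*. Report pH separately, as a bedside test of gastric placement against the same X-ray location. That keeps the wider aim of verifying correct placement in view, including esophageal tubes, which are reference-negative for the airway target.

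The cost is a small change of analysis wording. X-ray, location and pH are all already in the planned data collection, so no new data are needed. The change does not cure the small number of airway tubes behind the sensitivity estimate, which is a separate problem.

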### Pilot study

To understand the feasibility of the methods used in this study, we will conduct a pilot study before committing to the fidelity required for this multicentre study. We will select three cases in each in-patient setting, AED, and ICU. The ward nurses and DNs will perform NGT insertions and tests strictly according to the prespecified procedures. Besides participants’ demographic and clinical data and the results of the index test and reference tests specified in the data collection form, quantitative process measures and qualitative reviews will be used to establish the feasibility of the study.

The following process will be evaluated: DNs’ and ward nurses’ adherence rate to the protocol, total time used (from capnography calibration to receiving the results of the reference tests), and cost of the index test and the reference tests. The experiences of participating in the test of the DNs and ward nurses will be collected through semi-structured interviews with questions on the performance and completeness of the procedures and tests, feasibility of the procedures and tests, and usability of the capnography, pH test, and X-ray.

### Ethical considerations

The research team will protect participants’ rights and safety by adhering to local laws, Declaration of Helsinki, institutional policies, and ICH-GCP. There will be an emphasis on voluntary participation, and participants will be informed they can withdraw at any time from the study without consequences. Agreement will be made in advance with personnel in charge of the study venues for arranging participant recruitment. Before the study, participants will be informed of study details and asked to sign an informed consent form (See S2 File, information sheet and consent form for patients). If a potential participant lacks capacity to consent due to an acute illness or medical conditions that impairs cognition, the patient’s next of kin will be contacted, provided with a thorough explanation of the potential risks, benefits, and procedures of the study and will be asked to sign an informed consent form. The reasons why the patient is unable to provide consent (e.g., patient is non-responsive due to a medical or surgical condition or medication administered to treat the conditions) will be documented in the research file/chart and reviewed by the principal investigator and co-investigators. The patient and patient’s next of kin may withdraw from the study at any point, and their informed refusal will result in immediate data deletion.

All data collected will be kept confidential and used solely for this study. After data collection, the DNs of each study venue will store the raw data in a password-protected file and send it to the lead principal investigator (PI). Other researchers in the research team who want to use the data will need to be authorised by the lead PI and sign a data-sharing agreement. All electronic documents will be encrypted and stored in password-protected files, and all paper documents will be locked securely.

All identity information including the names and identity card number of the patients will not be collected. Each participant will be assigned an identity number. The data will also be analysed anonymously. All DNs will be trained and reminded on the importance of confidentiality and safe keeping of the data. They will be asked to sign a confidentiality pledge which highlights the importance of using appropriate safeguards to protect the confidentiality of the information contained within the data set. No attempt will be made to contact individuals or family members of individuals whose information is contained in the data set.

This study has received ethical approval from The Joint Chinese University of Hong Kong–New Territories East Cluster Clinical Research Ethics Committee (CREC Ref. No.: 2022.073), Hospital Authority Central Institutional Review Board (Ref. No.: CIRB-2023-030-4), and Institutional Review Board of the University of Hong Kong/Hospital Authority Hong Kong West Cluster (IRB Ref. No.: UW23-332). Any amendments to the protocol will be sought from the research ethics committees.

## Discussion

This study is aimed at determining the diagnostic accuracy of ETCO_2_ detection using capnography in verifying the correct placement of NGTs among adult patients in hospital settings. Ensuring the correct placement of NGTs is a necessary and important step to ensure patient safety. Despite the various methods examined in literature for verifying NGT placement, the diagnostic accuracy of these methods is still suboptimal and often compromised by different patient- or equipment-related factors such as availability of aspirates or conditions of the test devices [7,16,17]. This study will provide evidence on the diagnostic accuracy of capnography in verifying NGT placement, and its applicability to patients in hospitals settings, evidence of which is limited in the current literature.

In this study, capnography will be examined in combination with the reference standards, including radiography and testing for pH values in gastric aspirates. This examination approach will identify the optimal combination of test results in verifying the correct placement of NGTs. A multicenter, observational trial of 85 patients undergoing general anaesthesia, orotracheal intubation and mechanical ventilation has suggested using a ETCO_2_ cutoff value of 25.5 mmHg for NGT tracheal misplacement and a pH cutoff value of 4.25 for NGT correct gastric placement for achieving a higher level of accuracy in determining gastric placement of NGTs [27]. Indeed, given that the use of ETCO_2_ may be limited in merely differentiating between tracheal and GI placement of NGTs, the use of more than one index test could be superior in increasing the diagnostic accuracy. This study will help determine a fast and effective method for detecting NGT placement in the respiratory tract, which is crucial to preventing respiratory complications associated with misplaced NGTs. Furthermore, an algorithm illustrating the decision making based on the results of these tests can be developed to guide practice. The results of this study will also inform the update of clinical practice guidelines regarding the recommendations across the Hospital Authority Hong Kong in verifying NGT placements in acute and rehabilitative settings.

Building on the results of this study, further studies can be initiated to examine the cost-effectiveness of ETCO_2_ detection. Qualitative evaluation of healthcare professionals’ feedback on using this method and exploration of patient experiences would be necessary to better understand the applicability of the method. More studies designed to test this method’s diagnostic accuracy in verifying tube location before each use, and among people with continuous feeding, would also be worthwhile. The results will provide valuable evidence in informing stakeholders’ decisions on the adoption of ETCO_2_ detection as a routine method for verifying NGT placement.

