**Discussion:**

This study will provide evidence on the diagnostic accuracy of capnography in verifying NGT placement and its applicability to patients in hospitals settings, since this evidence is limited in the current literature. In addition, it will help identify the optimal combination of tests in verifying the correct placement of NGTs and inform the update of clinical practice guidelines and stakeholders’ decisions on the adoption of ETCO_2_ detection as a routine method for verifying NGT placement.

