## Materials and methods

### Study design

A prospective observational diagnostic study will be conducted to assess the sensitivity and specificity of capnography in detecting the correct placement of NGTs using the reference standards of radiography and measurement of aspirates for pH value. This study was registered with ClinicalTrials.gov (ID: NCT05817864). We reported this study protocol following the recommendations of the STARD (Standards for Reporting Diagnostic Accuracy) statement [20] and the SPIRIT (Standard Protocol Items: Recommendations for Interventional Trials) 2013 statement [21].

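### The Discussion promises the best combination of capnography with X-ray and pH, but the planned reference is built from X-ray and pH, so any such combination would be judged partly against itself

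*Protocol article*

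**What the plan says.** Capnography is the only index test (Test methods, Index test). X-ray and pH are both placed on the reference side: the Abstract says "The reference standards will be the X-ray performed and pH value of gastric aspiration (pH ≤ 5.5) after the index test", and Study design speaks of "using the reference standards of radiography and measurement of aspirates for pH value". The Reference standard section starts more narrowly, with "This study will use radiography (chest/abdominal X-ray) as the reference standard for determining the correct placement of NGTs", and then adds pH measurement, with 5.5 or below taken as gastric. The Data analysis section fixes the reference for the accuracy measures: they "will be calculated with reference to a combination of X-ray and aspirate pH test". It does not say how the two results are combined, and it names only capnography as the test being scored.

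The Discussion then says that "capnography will be examined in combination with the reference standards, including radiography and testing for pH values in gastric aspirates", and continues: "This examination approach will identify the optimal combination of test results in verifying the correct placement of NGTs". It adds that an algorithm can be built on these tests and that guidelines will be informed. The Abstract makes the softer statement that "it will help identify the optimal combination of tests in verifying the correct placement of NGTs".

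**The concern.** To rank combinations of tests, each must be compared with a truth label that none of them helped to create. Here both tests that would be combined with capnography also form the label, and no third, independent reference is named. A combination containing pH or X-ray therefore agrees with the reference partly by construction.

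At stake is the output the Discussion promises: a preferred combination, an algorithm and guideline input on a safety check. The useful bedside question is how well capnography and pH together perform against X-ray. It can be answered without circularity only if pH is kept out of the reference.

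**Working it through.** **The plan's own figure.** The target of 500 is not in dispute here. For a proportion of 0.90, an exact two-sided 95% interval whose larger half is at most 0.03 needs 492, close to 500, and 39 × 13 = 507. The point below is one of logic.

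**Step 1: what the reference forces.** Let C be an abnormal capnogram, H be pH above 5.5 and X be airway placement on X-ray. The composite rule is not stated, so take both simple forms.

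- *Reference positive if X or H.* Every reference-negative case has H negative. Among them, the rule C-or-H reduces to C, so pH false alarms disappear from its specificity. C-and-H can never be positive there, so its specificity is 1.
- *Reference positive if X and H.* Every reference-positive case has H positive. C-or-H then has sensitivity 1. C-and-H has exactly the sensitivity of C, so requiring an abnormal pH seems to cost nothing.
- *Reference X alone.* Combinations of C and H share nothing with the reference. C-or-X has sensitivity 1 by construction, and its specificity is that of C.

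**Step 2: an illustration.** None of these inputs is in the documents. Assume 5% airway placement; sensitivity/specificity of 0.98/0.999 for X-ray and 0.96/0.99 for capnography; pH sensitivity 0.95 and specificity 0.70 to 0.90 (10% to 30% of non-airway tubes above 5.5); and conditional independence. Entries are sensitivity / specificity, and ranges run from pH specificity 0.70 to 0.90.

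| Rule | True | Against X alone | Against X or H | Against X and H |
|---|---|---|---|---|
| C alone | 0.960 / 0.990 | 0.942 / 0.989 | 0.151–0.335 / 0.990 | 0.954–0.958 / 0.987 |
| C or H | 0.998 / 0.693–0.891 | 0.985–0.981 / 0.692–0.890 | 0.998–0.994 / 0.990 | 1.000 / 0.691–0.888 |
| C and H | 0.912 / 0.997–0.999 | 0.895 / 0.996–0.998 | 0.144–0.319 / 1.000 | 0.954–0.958 / 0.996–0.998 |
| C or X | 0.999 / 0.989 | 1.000 / 0.989 | 0.160–0.355 / 0.990 | 1.000 / 0.986 |

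One entry by hand, at pH specificity 0.70. The true specificity of C-or-H is 0.99 × 0.70 = 0.693. Against X-or-H, the reference-negatives are 0.95 × 0.999 × 0.70 = 0.66434 non-airway and 0.05 × 0.02 × 0.05 = 0.00005 airway. Apparent specificity is (0.66434 × 0.99 + 0.00005 × 0.04) / 0.66439 = 0.990.

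**Step 3: effect on ranking**, using sensitivity + specificity − 1, at pH specificity 0.70.

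- True: C-or-H 0.998 + 0.693 − 1 = 0.691; C-and-H 0.912 + 0.997 − 1 = 0.909; C alone 0.960 + 0.990 − 1 = 0.950.
- Against X-or-H: C-or-H 0.988, C-and-H 0.144. The order of the two combinations is reversed.
- Against X-and-H: C-and-H 0.950, C alone 0.941. Their true order is reversed.
- Against X alone: C-or-H 0.677, C-and-H 0.891, C alone 0.931. The true order is kept.

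**Step 4: sensitivity to prevalence.** At 2% airway placement, C-or-H still shows specificity 0.990 against X-or-H. C-and-H shows sensitivity 0.945 to 0.955 against X-and-H (true 0.912).

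The low sensitivity of C alone against X-or-H has a different cause: tubes outside the airway with pH above 5.5 are labelled positive. With airway rate π, rate q of pH above 5.5 in non-airway tubes and error-free X-ray, the pH-only share of reference-positives is (1 − π)q / [π + (1 − π)q]. It is 66% at π = 5%, q = 10%; 91% at π = 2%, q = 20%; and 94% at π = 2%, q = 30%. That concerns how the composite is defined and is separate from incorporation.

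**The case against.** The strongest reply is that combinations are not an objective. The Abstract's Objective, the closing aim of the Introduction and the opening of the Discussion all concern capnography alone. The combination statements stand in discussion text, the Abstract claims only to help, and the algorithm is only something that can be developed. This largely stands and limits the weight of the point. It does not remove it: the Introduction lists combinations among the gaps that motivate the study, and the main text says without qualification that the study will identify the best one.

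Second, a reader might infer that the combination question cannot be answered at all. The documents do not support that. Under Data collection, the capnography, X-ray and pH results and the tube's location are all recorded, and the Reference standard section itself begins with radiography. Capnography plus pH against X-ray is available and not circular. Combinations that include X-ray remain circular, whichever of these references is used.

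Third, the biased analysis is not one the article specifies, and a full protocol or analysis plan may exist. That is fair, so missing detail is not the complaint. The article itself fixes a reference containing both tests and promises a result that this reference cannot support.

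Finally, it is tempting to say that X-ray combined with anything is perfect when X-ray defines truth. Only one measure is forced: sensitivity for an either-positive rule, specificity for a both-positive rule. The other stays that of the partner test.

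**Conclusion.** The point holds for the plan as written: the reference in Data analysis and the combination promised in the Discussion use the same two tests, so combinations containing pH or X-ray cannot be ranked fairly. The logic needs no assumed figures. Its size and direction depend on the unstated composite rule. In the illustration, the distortion ranges from trivial (sensitivity of C-or-H 0.998 shown as 1.000) to large (specificity 0.69–0.89 shown as 0.99), and the order of rules can reverse. These values rest on assumed prevalence, test properties and conditional independence.

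A reader might also infer that the main estimate for capnography is biased by this. It is not: capnography is no part of the reference. Whether the composite labels airway placement well is a separate question. The point calls for a correction to the reference and to the claims. It does not invalidate the study's stated objective.

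**What to change.** 1. Make tube location on X-ray the sole reference. This agrees with the opening of the Reference standard section and needs matching amendments in the Abstract, in Study design, in the rest of the Reference standard section and in Data analysis.
2. Treat pH as a second index test, with no aspirate as its own result category, so that these participants are not lost through the exclusion of missing reference results.
3. Report four rules against X-ray, with exact confidence intervals: capnography alone, pH alone, either abnormal and both abnormal.
4. Keep any paired comparison descriptive. At an assumed 2% to 5% airway rate, 507 participants give about 10 to 25 airway cases. With the assumed sensitivities of 0.960 and 0.912, about 0.5 to 1.2 of them would be discordant between capnography alone and the both-abnormal rule (0.048 × 10.1 and 0.048 × 25.4).
5. Limit the combination statements in the Abstract and Discussion to the two bedside tests, or withdraw them.

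These changes concern the analysis and its claims, not how tubes are checked in practice. The cost is a small added analysis and a wording amendment, which the Ethical considerations section routes to the ethics committees. No new data are required.
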